**Figure 2 F2:**
[figure not shown]
Vision training panel kit (reprinted with permission by Formenti et al., 2019).

### 2.4 Measurements and procedures

#### 2.4.1 Anthropometric variables

Body height and mass will be measured to the nearest 0.1 cm and 0.1 kg, respectively, using a beam scale (SECA 220, Hamburg, Germany).

#### 2.4.2 Cognitive performance

Inhibitory control will be measured by the Flanker Task, previously used in ID individuals (Van Biesen et al., 2017) (Figure 3A). Participants will be requested to indicate the direction of a left- or right-pointing target arrow as quickly as possible while ignoring two flanking arrows on each side pointing in the same or opposite direction. The task includes two conditions: congruent and incongruent. The congruent condition consists of trials in which both the target arrow and the four flanking arrows are pointed in the same direction (left: <<**<**<< or right: >>**>**>>). The incongruent condition consisted of trials in which the flanking arrows point in the opposite direction of the target arrow (<<**>**<< or >>**<**>>). Participants have to press button A on the keyboard when the target arrow points to the left (i.e., <) and L when the target arrow points to the right (i.e., >). Two sets of 50 trials each will be randomly proposed. The mean response time of the correct responses and the percentage of correct responses will be computed for each condition as the outcome.

**Figure 3 F3:**
[figure not shown]
Testing procedures pictorial setting. **(A)** Cognitive performance, Flanker Task test. **(B)** Postural control, Modified Balance Error Scoring System. **(C)** Agility, Time Up and Go test. **(D)** Lower-body muscle strength, Five Repetition Sit-to-Stand test. **(E)** Upper-body muscle strength Handgrip Strength Test.

#### 2.4.3 Physical fitness

Different biomotor abilities will be measured and visually shown in multipaneled Figure 3. Postural control will be screened by the modified Balance Error Scoring System (M-BESS) performed in an upright stance while conserving stability in three positions for 20 s (i.e., bipedalism, tandem or monopodial) on a firm surface (Figure 3B). The examiner will count the person's errors while maintaining the proper stance (Azad et al., 2016).

The integration between the agility domain and cognitive performance will be assessed by the time up-and-go test (TUG) (Figure 3C). Outcomes of the TUG test are: (i) the time a participant takes to get up from a chair, to walk and turn around a cone positioned 3 m far away and to walk backwards to the chair again while carrying a full glass of water in one hand (Maranhão-Filho et al., 2011) and (ii) the number of times the participant spills water on the ground (Kachouri et al., 2024).

Lower-body muscle strength will be assessed using the five-repetition sit-to-stand (5STS) by asking the patient to rise and sit down for five consecutive repetitions with arms crossed over the chest. This procedure is particularly suited to patients with disabilities (Polidori et al., 2024). Performance time in seconds will be obtained using a stopwatch (Figure 3D).

Upper-body strength will be detected with the handgrip strength test (HST), with the patient sitting on a chair while exerting the maximum isometric grip (Mathiowetz et al., 1985) (Figure 3E). A Camry dynamometer (CAMRY EH101, Sensun Weighing Apparatus Group Ltd, Guangdong, China), which provided excellent validity and reliability among adult-aged community-dwelling individuals (Huang et al., 2022), will be used to detect the maximal handgrip strength.

It is worth noticing that for M-BESS, TUG, 5STS, and HST procedures, the same tester will conduct three trials while respecting an interval rest of 60 s to detect the consistency and reliability of the measures.

### 2.5 Statistical analysis

The sample-size calculation is established based on a previous study (Formenti et al., 2019) on the primary outcome (incongruent condition of the Flanker task) using G^*^Power software. From a priori power analysis, observing a sample size of up to 84 individuals (β = 0.9) is requested, respecting a large effect size (Cohen's f equal to 0.4) with a type I error rate of α = 0.05. All data will be presented as mean ± standard deviation. The dataset will be tested for normal distribution using Shapiro–Wilk's normality test. Based on the study's design, the primary independent endpoints are the treatment groups and time. A two-way (treatment × time) repeated measures ANOVA will be used on each outcome variable to determine the interaction between the three time points (baseline, 8 weeks, 16 weeks) and groups (VT, VTD, C). If an interaction exists, the simple effect and pairwise comparisons will detect differences between groups at each time point. Subsequently an additional age stratification and comparison will be performed to check any age-related difference. If a main effect is detected, data will be analyzed using a *post-hoc* analysis (Bonferroni test). The significance level will be set at *p* < 0.05. Partial eta squared (Part 2) effect size will be used to estimate the magnitude of the difference within each group, respecting a threshold for small (0.01), moderate (0.06) and large effects (0.14) (Cohen, 2013).

If the Shapiro-Wilk's normality test is not passed, non-parametric tests will be applied. The Friedman Test will be performed to detect differences between groups over time in both primary and secondary outcomes. In addition, to examine where the differences occur, a Wilcoxon Signed Rank test with Bonferroni adjustment will be used as a *post-hoc* analysis. Also, in these tests, the significance level will be set at *p* < 0.05.

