## Abstract

Aging leads to changes in motor-cognitive performance. Despite the importance of physical activity for healthy aging and the need for health promotion interventions in individuals with intellectual disability (ID), there is a lack of empirically strategies for promoting health in adults with ID. Therefore, we are conducting a clinical trial (NCT06628999 on clinicaltrials.gov) to investigate a strategy for promoting healthy aging by targeting physical and cognitive domains in ID individuals. The present work aims to provide a detailed account of the study protocol of the proposed trial to promote transparency and dissemination of the ongoing research. Specifically, this project will study the effect of a vision training program on cognitive performance and physical fitness in adults with ID. A secondary aim is to examine the association between mental and physical performance outcomes. Participants will be randomly allocated into a vision training group (VT, *n* = 28), a vision training-detraining group (VTD, *n* = 28), and a control group (C, *n* = 28). During the first 8 weeks, the VT and VTD groups will follow the same training protocol (based on vision oculomotor exercises combined with postural control exercises). From weeks 9 to 16, the VT group will continue the training protocol, whereas the VTD group will abstain from training (detraining). Cognitive performance and physical fitness will be assessed at baseline, mid- and post-training intervention. Overall, a vision training program can positively impact various aspects of life for individuals with ID promoting autonomy, and social integration to counteract the aging process.

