### 1.1 Study objectives

The overall main purpose of this research project is to determine the effectiveness of perceptual-vision training on cognition and physical functioning in individuals with intellectual disabilities.

Specifically, the primary endpoint is to identify the role of eye training on cognitive performance in terms of inhibitory control. The secondary endpoints are to verify the contribution of vision training on postural control, upper and lower body strength and agility outcomes. The tertiary endpoint aims to verify any potential effect of age, reinforcing the concept of promoting healthy aging.

Our primary hypothesis is that perceptual vision training intervention will promote a greater increase in cognitive and motor performance compared to the usual care control group. In addition, the secondary hypothesis is that a period of detraining could slightly attenuate the training-induced gains achieved during the previous intervention period. The third hypothesis is to detect whether there is an age-related effect on the outcomes measured.

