### 2.2 Study design

This project is a three-arm, parallel, randomized controlled trial. In detail, Figure 1 highlights the flow diagram of the overall design setting. At the beginning, participants will have their body mass and height measured. After that, a 1-week familiarization period will be implemented during which participants will adapt to the exercise techniques used throughout the study. Following 1 week of baseline testing, participants will be randomly assigned to three groups: (i) a Visual Training Group (VT, *n* = 28) that will perform oculomotor exercises combined with postural control exercises (Formenti et al., 2019) for 16 weeks; (ii) a Visual Training-Detraining group (VTD, *n* = 28) that will follow the same training protocol of VT for the first 8 weeks, abstaining from any training for the following 8-weeks period (from week 9 to week 16) and (iii) a control group (C, *n* = 28) in which no intervention will be implemented. Randomization will be achieved using a random-number generator (https://www.random.org using a 1:1:1 ratio) and to ensure adequate allocation concealment this procedure will be carried out by a blinded external researcher. An independent researcher will conduct the allocation sequence until the interventions are assigned. A research team collaborator will enroll and assign participants to the three groups. Baseline testing will be repeated after 8 weeks (mid-training testing) and at the end of week 16 (post-training testing).

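### VT and VTD are the same treatment until week 8, but the plan names no pooled week-8 contrast and does not adjust the follow-up comparisons for earlier scores: valid, but inefficient

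*Protocol article*

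**What the plan says.** The Abstract states: "During the first 8 weeks, the VT and VTD groups will follow the same training protocol". Section 2.2 (Study design) agrees: VTD stops training only from week 9, and each arm has 28 participants ("using a 1:1:1 ratio").

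Section 1.1 (Study objectives) makes superiority over usual care the primary hypothesis. On detraining it says that "the secondary hypothesis is that a period of detraining could slightly attenuate the training-induced gains". No effect size is given for that loss.

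Section 2.5 (Statistical analysis) tests "the interaction between the three time points (baseline, 8 weeks, 16 weeks) and groups (VT, VTD, C") in a repeated measures ANOVA. An interaction is followed by simple effects and pairwise group comparisons at each time point. Bonferroni is named as the post-hoc test where a main effect is detected. The section describes no contrast that pools VT with VTD, and no covariate. The sample size rests on "respecting a large effect size (Cohen's f equal to 0.4"), "with a type I error rate of α = 0.05", not tied to a named contrast.

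**The concern.** Up to week 8 the trial has in effect two treatments, training (56 people) and no intervention (28). The follow-up comparisons treat it as having three. The VT versus VTD comparison at week 8 answers no treatment question, and each training-versus-control comparison uses only half of the trained participants.

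The detraining question has a different weakness. VT versus VTD at week 16 is its randomised comparison, and the week-8 score is measured before the two arms diverge. That score can therefore be used as a covariate without bias, and it is likely to predict the week-16 score. The interaction test uses within-person change, but the stated follow-up at week 16 compares the groups at that visit without adjustment.

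At stake is precision on the primary and secondary hypotheses, and how a non-significant detraining result is read.

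**Working it through.** **Inputs.** Arm sizes 28, 28 and 28 (section 2.2). Alpha 0.05, f = 0.4 and total 84 (section 2.5). The printed β = 0.9 is read as power 0.9. Assumed, because the article does not give them: an illustrative week-8 effect of 0.6 SD, detraining losses of 0.2 and 0.49 SD, and a correlation ρ of 0.6 to 0.8 between week-8 and week-16 scores. Effects are in units of the between-person SD. Powers are two-sided, from the noncentral t distribution.

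**1. The plan's own figure.** For a one-way ANOVA with three groups, the noncentrality is λ = f²N = 0.16 × 84 = 13.44 on 2 and 81 df. Power is 0.907. With N = 81 it is 0.895, so 84 is the smallest balanced total that reaches 0.90. The stated size reproduces as a test of three groups at one time point.

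**2. Week 8, variance of training minus control** (in units of σ²):
- One pair: 1/28 + 1/28 = 2/28 = 0.0714.
- Mean of VT and VTD minus C, inside the three-arm model: ¼(1/28 + 1/28) + 1/28 = 3/56 = 0.0536.
- Information ratio: 0.0714 / 0.0536 = 1.333. The standard error falls by 1 − √0.75 = 13.4%.

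**3. Week 8, power at 0.05.** With VT = VTD = d and C = 0, f = d√2/3, so f = 0.4 corresponds to d = 0.4 × 3/√2 = 0.85.

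| Effect | 28 vs 28 | 56 vs 28 |
|---|---|---|
| 0.6 SD (illustrative) | 60% | 73% |
| 0.85 SD (plan's f) | 88% | 95% |

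The three-arm 2-df test at week 8 has 62% power at 0.6 SD and 91% at 0.85 SD, so the gain over that test is similar at 0.6 SD and slightly smaller at 0.85 SD.

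**4. Week 16, VT versus VTD, power at 0.05.** The 0.49 SD case takes f = 0.4 with means D, D/2 and 0. Then f = D√(1/6), D = 0.98, and half the gain is lost. Adjustment divides the residual SD by 1/√(1 − ρ²), so the effective size is d/√(1 − ρ²).

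| Loss | Unadjusted | Adjusted, ρ = 0.6 | Adjusted, ρ = 0.8 |
|---|---|---|---|
| 0.2 SD | 11% | 15% | 23% |
| 0.49 SD | 44% | 61% | 85% |

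The unadjusted 95% CI half-width is about 2.005 × √(2/28) = 0.54 SD. Multiplied by √(1 − ρ²) it becomes 0.43 SD at ρ = 0.6 and 0.32 SD at ρ = 0.8.

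**5. Does separating the arms cause the low detraining power?** No. VT and VTD must be separate to study detraining, and pooling them at week 8 leaves the week-16 comparison at 28 versus 28.

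**The case against.** The planned analysis follows the randomisation and is unbiased, and the three-arm model can itself supply the pooled contrast. Named contrasts and covariates are often left to an analysis plan that is not shown here. The first part stands: this is a matter of efficiency, not an error. The second stands only in part, because section 2.5 does state its follow-up comparisons, and what it states is less precise than the same data allow.

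Four stronger readings are tempting and are not supported:

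- *That the detraining contrast is nearly powerless, and that separating the arms makes it so.* Step 5 rules out the cause. The power depends on an effect the article never quantifies: at 0.8 SD the unadjusted contrast has 84% power. Any further gain in VT after week 8 would also enlarge the difference.
- *That the self-comparison at week 8 uses up part of a Bonferroni correction.* Section 2.5 attaches Bonferroni to a main effect and names no correction for the comparisons that follow an interaction. If it were applied over three pairs, a single pair at 0.6 SD would have 42% power. Setting that against 73% for the pooled test would mix the gain from pooling with the gain from dropping the correction.
- *That the authors plan to read non-significance as retained cognition.* Section 3 cites outside work to that effect in older adults, but it predicts some attenuation in VTD and calls for further research.
- *That two contrasts, pooled training versus C at week 8 and VT versus VTD at week 16, could replace all pairwise tests.* That would remove VT versus C at week 16, the control comparison for the 16-week programme named as the aim in section 1.

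**Conclusion.** The point holds as a low-cost improvement to a valid analysis. The 1.33-fold information gain at week 8 needs only equal arms and identical treatment to week 8. In power at 0.05 it is worth about 13 points at 0.6 SD and about 7 points at the plan's own effect size.

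For detraining, the gain depends on the assumed correlation, and the loss of half the gain is also an assumption. Adjustment helps materially for a moderate loss (44% to 61–85%). For a slight loss of 0.2 SD, which is nearer the article's wording, it does not rescue the comparison (11% to 15–23%). The estimate and its confidence interval should therefore carry that result, whichever analysis is used.

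One premise needs tidying. Section 2.3 describes both training groups as following four phases up to week 16, while the Abstract and section 2.2 have VTD stop after week 8. These passages must be reconciled. The week-8 argument is the same under either reading.

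**What to change.** Within the three-arm analysis in section 2.5, prespecify:

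- (a) Week 8: the mean of VT and VTD versus C, adjusted for baseline.
- (b) Week 16: VT versus C, adjusted for baseline, kept as the control comparison for the 16-week programme.
- (c) Week 16: VT versus VTD, adjusted for the baseline and week-8 scores, reported as a difference with a 95% CI, with a statement that non-significance will not be read as retention.

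Drop VT versus VTD at week 8. State how multiplicity across (a) to (c) is handled. If a detraining effect size of interest can be named, give the power of (c) for it.

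The cost is small: no new data or visits, a little more analysis work, and a multiplicity statement. If the chosen rule splits alpha across the contrasts, the powers above, all at 0.05, will be lower.

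### The contrasts that decide VT versus control are gated on the interaction test and carry no baseline adjustment: valid, but they give away power that a prespecified baseline-adjusted week-16 contrast would keep

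*Protocol article*

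**What the plan says.** Section 1.1 of the protocol article sets the primary hypothesis: the training "will promote a greater increase in cognitive and motor performance compared to the usual care control group". Under section 2.2, participants are tested at baseline, then randomised 1:1:1 to VT, VTD and C (28 each), and tested again at 8 and 16 weeks.

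Section 2.5 applies a two-way repeated measures ANOVA to each outcome "to determine the interaction between the three time points (baseline, 8 weeks, 16 weeks) and groups (VT, VTD, C". Its next step is: "If an interaction exists, the simple effect and pairwise comparisons will detect differences between groups at each time point". A later sentence provides Bonferroni post-hoc tests after a main effect. No baseline covariate and no change-from-baseline contrast is named. The primary outcome for sizing is the incongruent Flanker condition, with f = 0.4 and alpha 0.05: "observing a sample size of up to 84 individuals (β = 0.9) is requested". The 0.9 is evidently power.

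**The concern.** The hypothesis is about gain. The omnibus interaction, with (3 − 1) × (3 − 1) = 4 degrees of freedom, tests whether the arms change differently, but not which arm gained or when. The per-visit comparisons have to answer that, and on their natural reading they compare group means at one visit without the participant's own starting score.

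This has three consequences.

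- **Gate.** A real VT versus C difference at week 16 counts only if the 4-df test is also significant.
- **No adjustment.** Variation between participants that the baseline score could explain stays in the week-16 contrast.
- **Baseline tests.** Each time point includes baseline. Randomisation follows baseline testing, so a group difference there can only be chance.

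What is at stake is the chance of detecting the trial's main effect. The validity of the test is not in question.

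**Working it through.** **Inputs from section 2.5 and section 2.2.** Three arms of 28, three visits, f = 0.4, alpha 0.05, power 0.90.

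**Assumptions, not in the document.** Correlation rho between visits 0.3 to 0.7 (compound symmetry), normal data with SD 1, no missing visits, and Bonferroni for three pairs (0.05/3 = 0.0167) in the follow-up.

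**1. The plan's own figure.** For a one-way ANOVA with three groups, lambda = N × f² = 84 × 0.16 = 13.44 on 2 and 81 df, giving power 0.907. N = 81 gives 0.895. So 84 is the smallest balanced total reaching 90%, and f = 0.4 acts as a group effect at a single occasion. Read as a three-visit interaction effect, f = 0.4 would need 36 participants or fewer, so that reading does not give 84.

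**2. Effect for VT versus C.** With week-16 means d, d/2 and 0 for VT, VTD and C, f = d × √(1/6) = 0.408d. Hence d = 0.4/0.408 = 0.98 SD.

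**3. Precision.** The unadjusted week-16 difference has SE √(2/28) = 0.267 SD. Adjusting for baseline multiplies the variance by 1 − rho²: 0.91, 0.75 and 0.51 at rho 0.3, 0.5 and 0.7.

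**4. Power by simulation (10,000 runs per row).** Planned route: interaction p < 0.05 and then an unadjusted VT versus C t test at week 16. Alternative: ungated ANCOVA on the baseline score. Both use 0.0167. Two week-8 patterns are shown: half of d in both trained arms, or all of d.

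| Week-8 effect | rho | Gate passes, d = 0.98 | Planned, d = 0.98 | ANCOVA, d = 0.98 | Planned, d = 0.6 | ANCOVA, d = 0.6 |
|---|---|---|---|---|---|---|
| half | 0.3 | 73% | 68% | 90% | 20% | 46% |
| half | 0.5 | 88% | 79% | 95% | 24% | 53% |
| half | 0.7 | 99% | 88% | 99% | 33% | 74% |
| full | 0.3 | 93% | 83% | 91% | 26% | 46% |
| full | 0.5 | 98% | 87% | 95% | 31% | 55% |
| full | 0.7 | 100% | 88% | 99% | 38% | 74% |

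A repeat of the simulation gave 69% to 89% against 91% to nearly 100% at 0.98 SD, and 21% to 39% against 47% to 76% at 0.6 SD. The figures are good to about two points.

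**5. Where the loss arises (d = 0.98, half pattern).** Ungated and unadjusted, power is about 88% at any rho. At rho 0.3 the gate costs about 20 points (88% to 68%) and the missing adjustment about 2 (90% against 88%). At rho 0.7 the gate costs about 1 point and the missing adjustment about 11 (99% against 88%).

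**6. Without Bonferroni.** At 0.05 for both routes and d = 0.98, the planned route has 71%, 85% and 94% (half pattern, rho 0.3, 0.5, 0.7) against 96%, 98% and over 99%. In the full pattern it has 89%, 94% and 95% against much the same ANCOVA figures. The loss is then about 5 to 25 points.

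**The case against.** The strongest reply is that the interaction is itself a within-person test of differential change. Baseline is therefore used, and the omnibus test fits the hypothesis. That stands: only the gate and the follow-up contrasts are at fault.

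Second, the size depends on quantities the document does not give. At the protocol's own effect and rho 0.5 to 0.7, with a full effect by week 8, the planned route has 87% to 88%, close to the 90% target. It would be tempting to say the plan discards much of the trial's power, but that reading needs a smaller true effect such as 0.6 SD, which is not the protocol's assumption. Comparing a Bonferroni-adjusted planned test with a single 0.05 contrast would also inflate the gain, so both routes are held to one level here.

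Third, the article ties Bonferroni to a main effect, not to the interaction follow-up, so its use here is an assumption; the result without it is in step 6. The main-effect route also means the interaction is not the only path to post-hoc tests. A group main effect averages over baseline, however, so it does not test a greater gain at week 16.

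Two further inferences fail. A reader might conclude that anyone missing a visit is dropped. Classical repeated measures ANOVA usually does this, but the article states no missing-data rule, and one may stand in a document not shown. A reader might also say that chance baseline imbalance biases the week-16 contrast. Under randomisation it does not: the standard error already covers it, so it is the same loss of precision and not a second harm.

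**Conclusion.** The point holds as one of efficiency and of fit between hypothesis and contrast. The planned parametric analysis is valid, but its deciding comparisons are gated and unadjusted although the claim concerns gain. At the protocol's effect size the cost is about 8 to 22 points of power for VT versus C at week 16, at equal Bonferroni level. At 0.6 SD it is about 20 to 41 points (26% against 46%, up to 33% against 74%).

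These sizes rest on the assumed correlation, the assumed week-8 and VTD patterns, normality and complete data. The direction was the same in every scenario tried. The non-parametric branch, used if normality fails, is not covered by these figures.

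**What to change.** For the incongruent Flanker outcome, name as the primary analysis the baseline-adjusted VT minus C difference at week 16 with its 95% CI. Take it from an ANCOVA, or from a mixed model of the week-8 and week-16 scores with baseline score as covariate and arm by visit, in all randomised participants with follow-up data. Do not make it conditional on the interaction F-test. List the VTD contrasts, including the detraining comparison, as named secondary comparisons so that the second hypothesis keeps its place. Drop the between-group tests at baseline.

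This changes wording only; the baseline score is already collected. The price is committing in advance to one primary contrast. A mixed model would also use participants with a missing follow-up visit, which is a side benefit and not the reason for the change.

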**Figure 4 F4:**
[figure not shown]
Study protocol design setting.

In detail, the VT group is expected to improve outcomes of both cognitive and physical domains at the end of week 16. Conversely, the VTD group during the detraining period is expected to slightly attenuate the training-induced gains achieved during the previous 8 weeks. Indeed, a short-term detraining period (i.e., 8–12 weeks) appears sufficient to rapidly lose previously gained physical adaptations (Bosquet et al., 2013), probably due to an attenuation of motor unit recruitment (Lemmer et al., 2000). When investigating the potential mediators in the association between physical fitness and cognitive function, it seems that molecular changes along with adaptations in brain structure, function and emotional factors are less impacted by short interruptions in training when compared to traditional fitness parameters (i.e., muscular strength). As a result, a detraining period may still preserve cognition and executive functions in older adults (Rodrigues et al., 2020). However, further research is necessary to clarify the effects of detraining on the potential mediators associated with physical exercise and cognitive performance in individuals with ID. Moreover, regarding the secondary aim, a positive association between cognitive outcomes and physical fitness is another expected result, given the physiological deterioration observed in the ID population (Reguera-García et al., 2023; Hartman et al., 2015; Haynes and Lockhart, 2012). Lastly, as for the tertiary aim, the expected findings are an effect of age on visual stimuli and neural changes. Thus, it is plausible to hypothesize that older individuals with ID may obtain fewer cognitive performance benefits compared to younger individuals with ID due to neurophysiological changes associated with the aging process of the visual and cognitive systems.

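### The age hypothesis is about who gains less from training, but the planned age stratification and comparison is undefined and need not test it; a prespecified continuous-age modifier would be a cheap improvement

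*Protocol article*

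**What the plan says.** Three places in the protocol article bear on age.

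- Section 1.1 (Study objectives): "The tertiary endpoint aims to verify any potential effect of age, reinforcing the concept of promoting healthy aging". The third hypothesis there is worded as an age-related effect on the measured outcomes.
- Section 3 (Expected results and discussion) makes the tertiary aim directional: "older individuals with ID may obtain fewer cognitive performance benefits compared to younger individuals with ID".
- Section 2.5 (Statistical analysis) specifies a treatment by time repeated measures ANOVA for each outcome and then adds: "Subsequently an additional age stratification and comparison will be performed to check any age-related difference". It gives no cut point, number of strata, test or age term.

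The sample size in section 2.5 was set for the treatment effect on the primary outcome, not for any age question: "observing a sample size of up to 84 individuals (β = 0.9) is requested", with Cohen's f = 0.4. Section 2.2 gives 28 per arm; section 2.1 gives an age range of 40 to 70 years.

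**The concern.** Getting less benefit when older is a statement about how the training effect changes with age. Two natural readings of stratify and compare do not address it:

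- Comparing age groups on the outcome mixes any general age trend in performance, which would be present in every arm, with the effect of training.
- Testing the training effect separately in each stratum and comparing the verdicts treats a difference in significance as if it were a significant difference.

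A third reading, comparing the size of the training effect between strata, does address it, but cutting a continuous age range discards information.

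At stake is the tertiary conclusion. Healthy aging is the trial's rationale, and section 3 expects the results to inform exercise prescription guidelines. A statement that training works in younger but not in older people could then arise by chance or from an ordinary age trend.

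**Working it through.** **1. The plan's own figure.** One-way ANOVA with three groups, f = 0.4, α = 0.05, noncentrality N·f². Power is 0.895 at N = 81 and 0.907 at N = 84. So 84 (28 per arm) reproduces, reading the printed β = 0.9 as power. It is a sample size for the treatment effect only.

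**2. Stratum size (assumption).** The article does not fix the strata. Two equal strata give 28/2 = 14 per arm and 42 in total; three give 28/3, about 9 per arm. With f = 0.4 present in full in each of two strata, omnibus power per stratum is 0.60 instead of 0.907.

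**3. Comparing separate p-values.** Take VT versus C with the same true benefit of 0.75 SD in both strata. A two-sample t test with 14 per arm has power p = 0.48. The chance that exactly one of two independent strata is significant is 2p(1 − p) = 2 × 0.48 × 0.52 = 0.50. Simulation with a median split of uniform age gives 50% to 51%. With the omnibus test at f = 0.4 it is 2 × 0.60 × 0.40 = 0.48.

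**4. A valid between-stratum interaction test.** With 14 per cell, the standard error of the difference in effects is SD × √(4/14) = 0.535 SD. The overall VT versus C contrast has SD × √(2/28) = 0.267 SD, so the interaction's is twice as large. For 80% power the effects must differ by (1.960 + 0.842) × 0.535 = 1.50 SD.

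**5. Information kept by a median split.** Under a linear trend this is the squared correlation between age and the split indicator.
- Uniform age on (−1, 1): mean absolute value 0.5, SD 1/√3, so (0.5 × √3)² = 0.75.
- Normal age: 2/π = 0.64.

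**6. Power for the interaction, continuous age versus median split.** Simulated VT versus C, 28 per arm, age assumed uniform over 40 to 70, average benefit 0.75 SD, benefit falling linearly with age:

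| Benefit at age 70 | Continuous | Median split |
|---|---|---|
| Half the average (0.375 SD) | 12% | 10% |
| Zero | 32% to 35% | 25% to 26% |
| −0.19 SD | 48% to 50% | 36% to 38% |
| −0.50 SD | 72% to 73% | 57% to 58% |

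Ranges cover repeated runs. The last two rows imply that training harms the oldest participants, which goes beyond the discussion's wording of fewer benefits. The first two rows are the relevant ones. With no age gradient, both tests hold their level (about 5%).

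**7. Which model term.** The planned model includes baseline as one of its three time points, so training gain is the treatment by time interaction. An arm by age term in that model tests whether age changes the arm difference averaged over all visits, baseline included. Modification of the gain is arm by time by age, with 2 × 2 × 1 = 4 degrees of freedom for three arms, three visits and linear age. The single-contrast equivalent is arm by age for VT versus C at week 16, adjusted for baseline.

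**The case against.** The strongest reply is that the article does not commit to a wrong test. The comparison is undefined and could be a between-stratum test of the training effect, which is valid and has the correct error rate. A reader might infer that the plan will produce misleading subgroup contrasts; the text does not support that. The 50% discordance applies only if separate p-values are compared, which the article never says. That part of the objection stands.

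Three further points also stand:

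- About 14 per arm per stratum is not in the document. It assumes two equal strata, and dropout or more strata would lower it.
- Section 1.1 taken alone allows a plain age effect on outcomes, which a stratified comparison could answer. The interaction reading rests on section 3.
- At gradients that fit the discussion's wording, continuous age gains little power.

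It can also be said that cut points and test details may sit in a fuller document, and that this is a tertiary, additional analysis. That limits the weight of the point but does not remove it. The article already names stratification as the method, and its objectives and discussion pose different age questions.

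**Conclusion.** The point holds in a limited form. Sections 1.1 and 3 do not state the same age question, and section 2.5 names a method that is not tied to either. Two of its three plausible readings would not test the hypothesis in section 3. The p-value reading would give discordant strata in about half of trials under identical effects of 0.75 SD, assuming two equal strata. The third reading is valid but gives up about 25% (uniform age) to 36% (normal age) of the information, assuming a linear trend and a median split.

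A reader might also infer that modelling age continuously would make the question answerable. It would not. With 28 per arm, power stays at about 12% to 35% unless the gradient is so steep that the oldest are harmed. The age analysis is exploratory under either method. The primary treatment comparison is not affected, so this is a cheap improvement rather than a critical fault.

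**What to change.** 1. State one age estimand in sections 1.1 and 3: how the training gain changes with age.
2. In section 2.5, replace the stratification with a single prespecified test of age in years, centred, as a modifier of that gain. Use either arm by time by age in the repeated measures model, or arm by age for VT versus C at week 16 adjusted for baseline. The second is simpler and gives one degree of freedom.
3. Report the estimated benefit at illustrative ages, for example 45, 55 and 65 years, with 95% confidence intervals, and label the analysis exploratory.
4. If strata are still displayed, fix the cut points in advance and do not compare their separate p-values.

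The cost is a few sentences, with no extra participants or measurements. The downside is an assumed roughly linear age trend, which a plot can check, and a test that remains underpowered unless the gradient is large.
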